## Abstract

**Background:**

In conventional multi-trauma care service (CTCS), patients are admitted to hospital via the accident & emergency room. After surgery they are transferred to the IC-unit followed by the general surgery ward. Ensuing treatment takes place in a hospital's outpatient clinic, a rehabilitation centre, a nursing home or the community. Typically, each of the CTCS partners may have its own more or less autonomous treatment perspective. Clinical evidence, however, suggests that an integrated multi-trauma rehabilitation approach ('Supported Fast-track multi-Trauma Rehabilitation Service': SFTRS), featuring: 1) earlier transfer to a specialised trauma rehabilitation unit; 2) earlier start of 'non-weight-bearing' training and multidisciplinary treatment; 3) well-documented treatment protocols; 4) early individual goal-setting; 5) co-ordination of treatment between trauma surgeon and physiatrist, and 6) shorter lengths-of-stay, may be more (cost-)effective.

This paper describes the design of a prospective cohort study evaluating the (cost-) effectiveness of SFTRS relative to CTCS.

**Methods/design:**

The study population includes multi-trauma patients, admitted to one of the participating hospitals, with an Injury Severity Scale score > = 16, complex multiple injuries in several extremities or complex pelvic and/or acetabulum fractures. In a prospective cohort study CTCS and SFTRS will be contrasted. The inclusion period is 19 months. The duration of follow-up is 12 months, with measurements taken at baseline, and at 3,6,9 and 12 months post-injury.

Primary outcome measures are 'quality of life' (SF-36) and 'functional health status' (Functional Independence Measure). Secondary outcome measures are the Hospital Anxiety & Depression Scale, the Mini-Mental State Examination as an indicator of cognitive functioning, and the Canadian Occupational Performance Measure measuring the extent to which individual ADL treatment goals are met. Costs will be assessed using the PROductivity and DISease Questionnaire and a cost questionnaire.

**Discussion:**

The study will yield results on the efficiency of an adapted care service for multi-trauma patients (SFTRS) featuring earlier (and condensed) involvement of specialised rehabilitation treatment. Results will show whether improved SFTRS logistics, combined with shorter stays in hospital and rehabilitation clinic and specialised early rehabilitation training modules are more (cost-) effective, relative to CTCS.

**Trial registration:**

Current Controlled Trials register (ISRCTN68246661) and Netherlands Trial Register (NTR139).

## Introduction

In the Netherlands, with a population of approximately 16 million people, every year about 99.000 persons are admitted to hospital after an accident, whereas 880.000 people visit the Accident & Emergency department (A&E) after an accident [1]. These accidents lead to considerable societal costs. Direct medical costs are estimated at 1 billion Euro/year, i.e. 3–4% of the total Dutch health care budget. Production losses due to acute trauma are estimated at 4 billion Euro, thus widely surpassing costs of chronic illness like cardiovascular diseases and cancer [2-4]. Many of the patients have multiple fractures. Major causes of multi-trauma are traffic accidents, accidents at work, (extreme) sports, falls, blasts, etc. [5]. The legs (incl. pelvis) are most frequently injured in multi-trauma [6-9]. Multi-trauma occurs more often in males and in younger adults [5]; [10]. Many patients are at an age where they have a paid job. Furthermore, the rehabilitation of the multi-trauma patients may take a long time. The societal impact of multi-trauma is therefore large.

Medical care for trauma patients is a combined responsibility of hospitals, ambulance services, trauma centres, rehabilitation clinics and GHOR (medical assistance after accidents and disasters). This co-operation between teams of specialists is called 'trauma care chain' (TCC). In the present study multi-trauma is defined as having 2 or more injuries of which at least 1 is life threatening, including trauma with an Injury Severity Scale (ISS) score > = 16; complex multiple injuries on both lower extremities; a combination of 1 upper and 1 lower extremity injury, the latter of which can not be used in load-bearing; or complex pelvis/acetabulum fractures. Several tools for rating trauma severity have been designed [11]. The ISS [12,13] is used most often.

In conventional multi-trauma care service (CTCS) each of the partners has its own more or less autonomous treatment perspective, depending on the professional's individual treatment views and experience. Clinical evidence, however, suggests that an integrated multi-trauma rehabilitation service approach or 'Supported Fast track multi-Trauma Rehabilitation Service' (SFTRS), featuring:

1) Earlier involvement of the rehabilitation physician in the hospital;

2) shorter stay in hospital and earlier transfer of multi-trauma patients to a specialised trauma rehabilitation unit;

3) an earlier start of both specific physical and psychosocial treatment provided by a multidisciplinary team;

4) early individual goal setting;

5) early start of psychological and social counselling;

6) an integrated co-ordination of treatment between the trauma surgeon and the rehabilitation physician, and

7) a shorter stay in a trauma rehabilitation unit

may be more (cost-) effective. Such SFTRS approach may lead to less secondary complications associated with immobilisation, which would negatively influence recovery and quality of life. Early personalised goal setting and early treatment of depression are known to positively affect outcome. SFTRS may lead to faster reintegration into society. Early return to work and active support from the multidisciplinary rehabilitation team will lead to a more stable social network, and the patient becoming less reliant on professional care in the long term. Also, the SFTRS may reduce the length of stay of multi-trauma patients in a hospital. Furthermore, earlier rehabilitation treatment in a specialised rehabilitation unit may also reduce the length of stay in the rehabilitation clinic, thus reducing costs of hospital/clinic consumption. At this moment it is not possible to make a precise calculation of these savings. Since earlier discharge also means that patients take part in society and work earlier, costs related to production losses and patient & family costs are expected to be lower.

The main objective of this study is to examine the effectiveness, costs and cost-effectiveness of an integrated care service for multi-trauma patients, called 'Supported Fast track multi-Trauma Rehabilitation Service' or SFTRS.

The general research question is:

Which of 2 rehabilitation services, i.e. 'Conventional multi-Trauma Care Service' (CTCS) or 'Supported Fast track multi-Trauma Rehabilitation Service' (SFTRS), is most (cost-) effective from a societal point of view?

Sub-questions are:

- What are the effects of the SFTRS on generic quality of life in multi-trauma patients as compared to the CTCS?

- What are the effects of the SFTRS on functional health status as compared to the CTCS?

- What are the costs to health care and to society of the SFTRS as compared to the CTCS?

- What is the cost-effectiveness of the SFTRS as compared to the CTCS?

The general hypothesis of this study is that SFTRS is more (cost-) effective than CTCS.

## Methods

### Design

This study is a prospective, multi-centre, non-randomised clinical trial in which two multi-trauma rehabilitation services will be contrasted, i.e. 'Conventional Trauma Care Service' (CTCS) and 'Supported Fast track multi-Trauma Rehabilitation Service' (SFTRS). The patients will be followed for 12 months (see flow chart, Figure 1). The inclusion time is 19 months.

**Figure 1 F1:**
[figure not shown]
**Flow chart of the study**. SFTRS: Supported Fast track multi-Trauma Rehabilitation Service; CTCS: Conventional multi-Trauma Care Service; A&E: Accident and Emergency department.

Prior to participation, informed consent will be obtained from all participants.

All protocols used in this study have been approved by the Medical Ethics Committee of the Rehabilitation Foundation Limburg in Hoensbroek, the Netherlands.

This study is registered at the Current Controlled Trials register (ISRCTN68246661) as well as at the Netherlands Trial Register (NTR1391).

### Population

Multi-trauma patients admitted to one of the accident & emergency departments (A&E) of the participating hospitals are included. Multi-trauma is defined as having at least 2 or more injuries of which at least 1 is life threatening, including a) trauma with an Injury Severity Scale score ISS > = 16, b) complex multiple injuries on both lower extremities, c) a combination of one upper and one lower extremity injury, the latter of which can not be used in load-bearing, or d) complex pelvis/acetabulum fractures (for in- and exclusion criteria see Table 1)

**Table 1 T1:** Inclusion and exclusion criteria

Inclusion criteria	Age > = 18 years
	Multi-trauma (as defined above)
	Hospitalisation after A&E admission
	Rehabilitation indication, i.e. lasting impairments or handicaps are expected
	Adequate Dutch language skills
Exclusion criteria	Severe alcohol and/or drug abuse
	Severe psychiatric problems

A&E: Accident and Emergency room

Participants for the SFTRS will be recruited in the adherence of the trauma centre in the south of the Netherlands. The reference group will be recruited in the adherence of one of the other trauma centres in the Netherlands. The inclusion of the participants will start in October 2008 and will continue until May 2010. Both medically and ethically it is not feasible to randomise the acute multi-trauma patients across the two trauma centres mainly due to geographical distances. Therefore, a non-randomised controlled clinical trial is used.

Based on the 2005–2007 databases from the participating centres, the influx numbers for the SFTRS group and the CTCS group are expected to amount to about 364/year and 370/year respectively. Prospective data from a pilot study in 2008 showed that, within 3.5 months, in each of the two centres 86 multi-trauma patients were admitted to the A&E. Given an inclusion period of 19 months, approximately 467 patients in each of the respective regions are expected, totalling 934 for this study (see flow chart, Figure 1).

To date, no exact data on differences in quality of life outcome between different treatment services for multi-trauma patients are available. Czyrny and co-workers [14] report an improvement in motor FIM score of 30.2 in a small group of bilateral lower limb multi trauma patients having received both hospital and subsequent rehabilitation treatment, at a mean length of stay of 62.8 (+/-6.0) days. In order to detect a difference of 15% of such improvement in FIM score between SFTRS and CTCS at T1 (assuming a two-sided significance level of 0.05, a power of 80%, and a common standard deviation (sd) of 9.5 as reported by Czyrny [14]), 71 persons per group are needed. Taking into account a 15% loss to follow-up, the required sample size is 82 persons per group (164 persons in total).

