### Statistical analyses

In non-randomised comparative studies, variations in case mix between centres can influence the interpretation of outcome data [48]. Therefore, for each of the data sets collected at T1 through T4, differences in outcome variable between the 2 services will be tested using multiple MANCOVA's, entering various indicators of case mix as co-variates, i.e. age, gender, ISS, number of complications, pre-trauma psycho-social status.

When patients drop out of the study, the reason for their withdrawal will be recorded. Drop-outs may bias the treatment effect evaluations. Therefore, the following regime will be applied:

- Missing T4 measurement: 'last-observation-carried-forward' principle will be applied.

- Missing T3 or T2 measurement: linear interpolation of data using data from adjacent time points (e.g. T1 and T4) for imputation.

- Missing T0 or T1 measurement or more than 2 missing measurements: discarding of patient data and influx of additional patient in order to meet n = 82 per group.

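### The target of 82 per group is slightly too low for the stated 15% loss, and it is used both as an enrolment number and as a number retained after replacement

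*Protocol article*

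**What the plan says.** The sample-size paragraph under Population starts from a cited report of "an improvement in motor FIM score of 30.2". It sets out to "detect a difference of 15% of such improvement in FIM score between SFTRS and CTCS at T1". The test is two-sided at the 5% level with 80% power, and the spread in both groups is taken from the same report as "a common standard deviation (sd) of 9.5". From this it concludes that "71 persons per group are needed". It then adds the attrition step: "Taking into account a 15% loss to follow-up, the required sample size is 82 persons per group (164 persons in total"). In that sentence 82 already contains the expected losses, so it is a number to enrol.

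The missing-data rules under Statistical analyses use the same figure differently. Patients without a T0 or T1 measurement, or with more than two measurements missing, are discarded, followed by "influx of additional patient in order to meet n = 82 per group". In that sentence 82 is reached only after the losses have been made good, so it is a number retained.

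**The concern.** There are two linked problems with one figure.

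First, an allowance for a 15% loss means that 85% of those enrolled must equal the number needed, so the base is divided by 0.85. The stated 82 is below the result of that division.

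Second, the losses covered by the allowance and the losses that trigger replacement overlap. The calculation is powered at T1, and a missing T1 is one of the grounds for discarding and replacing a patient. If 82 already includes an allowance for such patients, replacing them up to 82 allows for them again.

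What is at stake is chiefly clarity about when enrolment ends and how many patients the analysis is planned on. The effect on power is small.

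**Working it through.** **Inputs** (all from the Population section): reference improvement 30.2 motor FIM points; target difference 15% of this; SD 9.5; two-sided alpha 0.05; power 80%; loss to follow-up 15%; equal groups.

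**Step 1: reproduce the base figure.**
- Difference: 0.15 x 30.2 = 4.53.
- Normal approximation: n = 2 x (1.960 + 0.842)² x (9.5/4.53)² = 69.04 per group.
- Two-sample t-test: 70.01 per group, rounded up to 71.

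The stated 71 reproduces exactly with the t-test.

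**Step 2: the loss allowance.**
- Dividing: 71/(1 - 0.15) = 71/0.85 = 83.53, so 84 per group and 168 in total.
- Multiplying: 71 x 1.15 = 81.65, so 82 per group and 164 in total, which is the stated figure.
- Check on 82: 82 x 0.85 = 69.7, below 71. Put the other way, 82 tolerates a loss of 1 - 71/82 = 13.4%, not 15%.
- Check on 84: 84 x 0.85 = 71.4, which meets 71.

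**Step 3: power on each reading** (two-sample t-test, difference 4.53, SD 9.5).

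| Reading | Enrolled per group | Analysed per group | Power |
|---|---|---|---|
| Stated requirement | – | 71 | 80.6% |
| 82 enrolled, 15% lost, no replacement | 82 | 69.7 | 79.8% |
| 82 retained after replacement | about 97 | 82 | 85.9% |

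The enrolment of 97 is 82/0.85 = 96.5, rounded up. It assumes that the share of patients discarded equals the 15% loss to follow-up. The article does not give the discard rate, and some losses would not lead to discard: a missing T4 is carried forward, and a missing T2 or T3 is interpolated. If only 10% were discarded, for illustration, 82/0.90 = 91.1, so 92.

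**Step 4: the gap between the readings.** At 15% the two readings differ by 97 - 82 = 15 enrolled per group, or 30 in total, against a stated total of 164.

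**The case against.** The strongest reply is that the plan, followed as written, does not fall short at all. Anyone missing T1 is replaced until 82 is met, so 82 per group have T1 data, 11 more than the 71 needed, and power is 85.9%. This is correct. A reader might infer from the arithmetic that the trial misses its own target or is underpowered. The documents do not support that: the shortfall arises only if nobody is replaced, and the shortfall and the surplus are alternatives that cannot both occur.

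Even without replacement the effect is negligible. The t-test requirement is 70.01, so 71 is itself a rounding up over 0.01 of a patient. With 70 whole patients power is 79.99%, and on the normal approximation 69.7 patients give 80.4%. This also stands.

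The origin of 82 is an inference, because the article states no formula. A base of 70 would give 70/0.85 = 82.35, which rounds to 82 to the nearest integer. But the stated base is 71, and rounding up would give 83. Multiplication by 1.15 is the likelier source and is not established. The shortfall on the enrolment reading does not depend on it, since 82 x 0.85 is below 71 by any route.

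Finally, it can be said that sites do have an instruction, namely to replace until 82 is met, and that the inclusion period and about 467 expected admissions per region leave room. So it would be too strong to say that recruiters have no guidance. Those admissions are counted before eligibility and consent, but nothing in the article shows that 84 or 97 per group would strain them. What the reply does not remove is the conflict: one section counts the losses inside 82 and the other outside it.

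**Conclusion.** The point holds as a minor one, in two parts.

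- **Arithmetic.** Read as an enrolment number, 82 is 2 per group (4 in total) below the 84 that the stated inputs require. The cost is less than one percentage point of power: 79.8% at 69.7 analysed, against 80.6% at 71.
- **Double meaning.** This is the part with more practical weight. Neither reading makes both sections right. If 82 is enrolled, it should be 84 and the replacement rule names the wrong target. If 82 is retained, the 15% has been allowed for twice and the implied enrolment, about 97 per group, is not stated.

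Power is about 80% on one reading and about 86% on the other, so the trial's ability to detect the planned difference is not in question here. A reader might also conclude that the replacement clause should be removed. The arithmetic gives no reason for that: replacement is what keeps the number with T1 data above 71. Whether discarding and replacing patients could bias a non-randomised comparison is a separate question, not settled by this check.

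The figures rest on the article's own difference, SD, alpha and loss rate, on an unadjusted two-sample t-test, and, for the 97, on a discard rate of 15%.

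**What to change.** Give the target one meaning and use it in both the Population and the Statistical analyses sections.

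- **If it is an enrolment number:** restate it as 84 per group (168 in total) to leave 71 evaluable. Alternatively keep 82 and state that about 70 are expected to be evaluable, with power just under 80%. Then reword the replacement rule so that it no longer names 82 as the number to be met after discards.
- **If replacement is kept:** state the evaluable target and the enrolment it implies at 15% discarded. This is either 71 evaluable with about 84 enrolled per group, or 82 evaluable with about 97 enrolled per group and power of about 86%.

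In either case, state the formula used for the loss allowance. The cost is a correction of a sentence or two. The first option adds at most two patients per group. Keeping 82 as the evaluable target commits the trial to about 15 more per group than a plain reading of the Population section suggests.

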### Interventions/services

Supported Fast track multi-Trauma Rehabilitation Service

SFTRS involves the following:

a) The rehabilitation physician from the rehabilitation centre is routinely involved at a very early stage post-trauma. This allows an early start for multidisciplinary rehabilitation treatment;

b) Early transfer (within five days after having been added to the waiting list from the rehabilitation centre) to a centralised, specialised trauma rehabilitation unit equipped with facilities for early training programs;

c) Early individual rehabilitation goal setting;

d) Close co-operation and exchange of views and experiences between the trauma surgeon and the rehabilitation team by, for example, monthly clinical sessions and individual patient visits by the trauma surgeon in the first weeks after discharge;

e) Well-documented treatment protocols for multi-trauma patients for both the hospital and rehabilitation centre phases.

Three phases can be identified in the treatment of multi-trauma patients:

1 Early rehabilitation phase

2 Stage II rehabilitation phase

3 Discharge or post-discharge phase

#### - Phase 1: Early rehabilitation phase

In the early rehabilitation phase, the patient is not allowed to mobilise weight bearing. Consequently, the physiotherapist is concerned with maintaining joint mobility, muscle strength, sitting balance, condition and training transfers as well as treatments with non-weight-bearing conditions such as hydrotherapy and non-weight-bearing gait training. There are 10 sessions per week of 30 minutes each. In addition, fitness, gymnastics, table tennis, swimming, bowling, hand bike, wheelchair training, and archery are given. There are 2–3 sessions per week for each treatment modality of 60 minutes each. The occupational therapist advises on bed posture, mattress types, aids for independent daily self-care, wheelchair-dependency training and meaningful activities that can be performed while wheelchair-bound. In addition, the wheelchair accessibility and wheelchair friendliness of the patient's home are studied. If necessary, written and oral advice on temporary and long-term adaptations to the home is given and support is given and the patient is helped to apply for financial support so that the patient can return home as soon as possible. At first, this would be for a day or two at the weekend, supervised by an occupational therapist, but would later become permanent. With regard to work, the patient's job is analysed and the patient's workplace is visited. There are 4 sessions per week of 30 minutes each. The social worker and the psychologist will see every multi-trauma patient within the first week after admission. The social worker helps the patient to return home by dealing with the family and offering advice and support to the patient on financial matters, transport facilities. The social worker also contacts the employer and company doctor to look into the possibility of reintegrating the patient into their present job. The psychologist will examine the patient with regard to such conditions as mood disorders, posttraumatic stress syndrome (PTSS), acceptance problems and cognitive problems. The latter requires extensive neuropsychological testing. In addition, individual and group psychological counselling and specialised treatment for PTSS are given. If necessary, the rehabilitation specialist can refer the patient to a consultant in psychiatry, a consultant in neurology, a consultant in internal medicine, a consultant in rheumatology and/or a consultant in urology, who is affiliated to the rehabilitation centre.

#### - Phase 2: Stage II rehabilitation phase

In the Stage II rehabilitation phase, new treatment aims are added by the physiotherapist. These might include a gradual individual weight bearing scheme, co-ordination training and functional training. There are 7 therapy sessions per week of 30 minutes. In addition, fitness, gymnastics, table tennis, swimming, rowing, cycling and archery are given. This is offered in 2–4 sessions per week for each treatment modality of 60 minutes each.

The occupational therapist continues with the treatment goals as mentioned for phase I and trains the patient to perform household tasks, hobbies, etc in a home-like environment. There are three sessions per week of 30 minutes each. In addition, group therapies such as occupational therapy and recreational therapy are given 2–4 times per week each.

The social worker and the psychologist continue the work mentioned in phase I, depending on the individual needs of each patient.

